### Intervention

We will be comparing a standard information condition to an information plus planning condition. The standard (comparison group) package will consist of Canada’s physical activity guidelines [8] recommending 60 minutes of activity a day in bouts as short as five to ten minutes for children and a breakdown of ways for the family to achieve this physical activity (structured, unstructured, endurance, strength, activities, less than 60 minutes of sustained sedentary activity, reduce screen viewing by 30 min per day) commensurate with this guide. This will include the insert by CSEP [8]. The intervention also includes an adapted information booklet that we designed that emphasizes the benefits of physical activity and provides some strategies for working through common barriers to being active. The intervention condition will receive the same guidelines as the comparison condition but will also be provided with family physical activity planning material. This material will include skill training content (workbook how to plan for family physical activity) and practical material to create a plan (i.e., a colorful dry erase wall calendar for family activities with fridge magnets). The skill training material for planning is based on several streams of prior work in the adult physical activity literature. Families are instructed to plan for “when,” “where,” “how,” and “what” physical activity will be performed commensurate with the creation of implementation intentions/action planning [e.g., [26, 27]]. The workbook, however, also focuses on problem solving barriers to physical activity which is more akin to coping planning and traditional goal setting [28–31]. The design of all material was tested during implementation of the pilot and features graphic design and color images that represent family physical activity.

## Outcome measures

### Primary outcome measure

#### Change from baseline in children’s physical activity to 6 months

Children’s physical activity will be assessed at four separate time points: baseline, six-weeks, three-months and six-months. Children’s physical activity will be quantified by accelerometry. Children will wear a GT3X accelerometer on their right hip for a minimum of 10 hours per day for 7 days at each time point [32, 33].

### Secondary outcomes include

#### Parent’s physical activity

Parent’s physical activity will be quantified by accelerometry. Parents will wear an accelerometer for 7 days at baseline, six-weeks, three and six-months, for a minimum of 10 hours per day [33].

#### Motivation

Motivations for family based physical activity and personal physical activity will be measured using the constructs of the theory of planned behavior [15] including intention affective attitude, instrumental attitude, perceived control, adapted within the M-PAC framework [21]. Our measures of the theory of planned behaviour are validated from our previous research and have shown excellent predictive validity and internal consistency in adult [14, 16, 34] and child/adolescent [35] populations. These have been validated for both personal and family-based (i.e., activities as a family collective) physical activity [34]. Items will measure all components of the model (affective attitude, instrumental attitude, injunctive norm, descriptive norm, perceived control) including behavioural, normative, and control beliefs developed from prior pilot work in families. There will also be a measurement of habit [36] and identity [37] commensurate with the M-PAC model. The questionnaire will be completed by both parents and the target child. Change in motivation variables will be examined at baseline, six-weeks, three-months and six-months.

#### Self-reported family based physical activity and personal physical activity

All children will complete a modified version of the Physical Activity Questionnaire for Children (PAQ-C) [38] to assess habitual moderate to vigorous physical activity. The Godin Leisure-Time Exercise Questionnaire (LSI) will be used to measure self-reported physical activity in parents [39]. The LSI contains three questions, which assess the frequency of mild, moderate, and strenuous activity performed for at least 15 minutes during free time in a typical week. Self-reported physical activity will be examined at baseline, six-weeks, three-months, and six-months.

#### Health-related quality of life / psychosocial distress

Health-related quality of life / psychosocial distress will be assessed with parents using the Satisfaction with Life Scale [40]. The instrument is well-known and widely used.

Children’s Quality of Life will be assessed using the 5-item Satisfaction with Life Scale Adapted for Children (SWLS-C) [41]. The SWLS-C was adapted from the Satisfaction with Life Scale. The SWLS-C demonstrates a unidimensional factor structure and sound internal consistency [41].

#### Body composition

Skinfolds (triceps, biceps, subscapular, supra iliac, medial calf) will be measured using standard anthropometric procedures. Change in body mass index (BMI), waist circumference, and sum of 5 sites will be examined from baseline to 6 months (post-intervention).

#### Cardiovascular fitness

A steady-state walking treadmill test will be used to assess cardiovascular fitness in both parents and children. Heart rate, and blood pressure (sphygmomanometer and a stethoscope) will be monitored at rest and during exercise.

#### Musculoskeletal fitness

Grip strength, push ups, sit & reach flexibility, partial curl-ups, vertical jump and back extension will be measured to determine the musculoskeletal fitness of both the children and parents using the Canadian CSEP standardized protocols. Change in musculoskeletal fitness from baseline to 6 months (i.e., post-intervention) will be examined.

#### Demographics

A brief section in the baseline questionnaire will be used to assess characteristics including age, gender, marital status, ethnicity, level of education, health background, employment information, sleep habits, smoking habits, alcohol habits and general nutrition habits. We will use measures developed from a recently completed longitudinal study of parents [42].

The sole use of quantitative methods to understand the low physical activity in specific populations has been criticized. It has been suggested that other approaches be utilized to gain a more in-depth understanding of the issue [43–45]. Although quantitative measurement of outcomes will provide insight into the potency of our intervention, a process evaluation (whereby participants are interviewed) is also essential to examine the *content fidelity* (“what is done”) and *process fidelity* (“how it is done”) of program implementation [46]. Furthermore, as Plumer and colleagues [47] suggest, process evaluations “can help explain the program’s outcomes and identify ways to improve and/or replicate it. This will be accomplished through a member of the research team conducting a ten-minute interview with each family at the end of the study. Questions asked will start off broad asking the family to discuss the importance of family based physical activity, if they noticed any changes over the length of the study, and they move more specifically to the materials asking them what they liked/disliked about the study materials, what they found helpful/not helpful from the study materials and an opportunity to provide any additional thoughts or suggestions on what they felt could have been helpful to increase physical activity.

### Analysis strategy

Data will be evaluated for patterns of missingness for each psychosocial variable and behavior at all time points using the dummy coding procedures of Allison [48]. Depending on the outcome of these tests (e.g., missing at random, missing completely at random, etc.) we will initiate the appropriate missing data handling strategy. ITT analyses will also be performed in addition to sensitivity analysis procedures. Our first research question will be analyzed using a 2 (condition) x 4 (time) repeated measures factorial ANOVA on the primary outcome of child adherence. A child from each household in the eligibility range will serve for this analysis (chosen a priori through randomization procedures). Post hoc examinations using Tukey follow-up procedures will be utilized if necessary. Our secondary research questions (parent; parent/child; gender; season; fitness variables, etc.), will also be analyzed using a variant of this design with the addition of factors. Cluster analysis/HLM will be used for parent/child collinearity [49]. Our pilot study (r = .21) and prior research [10] suggests limited collinearity but it is appropriate to explore findings with these approaches given these are naturally clustered environments (i.e., family home) [49]. The qualitative analyses will incorporate the following processes [50, 51]: 1) Invite participants to review the transcripts of interviews, and summarize their perception of the data, for accuracy, and check for the trustworthiness of the data; 2) Conduct a thematic analysis using a reciprocal coding approach where researchers engage in open dialogue about themes and data interpretation. In doing so, each transcript is first reviewed independently, then through dialogue composite themes and related critical issues are developed; and 3) Manage the data using the NVivo software program. NVivo enables theory building, testing and elaboration. With NVivo, ‘free nodes’ can be created during the coding process, capturing participants’ perspectives and the investigators’ critical issues.

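### The missing-data method is picked from missingness tests, ITT is worded as an additional analysis, and the primary ANOVA has no stated population, so drop-out that differs by arm could bias it

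*Protocol article*

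**What the plan says.** Four statements in the Analysis strategy section of the protocol article matter here.

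- Missingness is examined first: "Data will be evaluated for patterns of missingness for each psychosocial variable and behavior at all time points using the dummy coding procedures of Allison".
- The result decides what is done next: "Depending on the outcome of these tests (e.g., missing at random, missing completely at random, etc.) we will initiate the appropriate missing data handling" strategy. No method and no decision rule is named.
- Intention to treat comes in the next sentence: "ITT analyses will also be performed in addition to sensitivity analysis procedures".
- The primary model follows: "Our first research question will be analyzed using a 2 (condition) x 4 (time) repeated measures factorial ANOVA on the primary outcome of child adherence". One child per family enters it: "A child from each household in the eligibility range will serve for this analysis (chosen a priori through randomization procedures".

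The section does not say whether the ANOVA covers all randomised families, only those with complete data, or an imputed data set. It mentions hierarchical models, but only for the clustering of parents and children.

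Elsewhere, Statistical power and sample size allows for 25% attrition, Randomization says that participants know their group, and Intervention gives the planning workbook and calendar to one arm only.

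**The concern.** Three features combine.

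First, the plan treats the missingness mechanism as something that tests can settle. Tests on observed data can give evidence against missing completely at random. They cannot tell missing at random from missing not at random, because that depends on the values that were not seen.

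Second, a classical repeated-measures ANOVA needs a full set of waves per child. Unless something is imputed beforehand, a child who misses the six-week week of wear is lost even if the six-month value was recorded.

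Third, describing ITT as something *also* done leaves open that the headline result comes from another population.

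Families know their arm and only one arm carries the planning task, so drop-out could plausibly differ by arm in rate or in reason. If it does, randomisation no longer protects a comparison of completers.

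**Working it through.** **Inputs from the article.** 160 families, 80 per arm, 25% attrition, type I error .05 and average correlation across time ρ = .75 (Statistical power and sample size); four waves (Primary outcome measure); 1:1 allocation known to families (Randomization).

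**Assumed, because the article gives no figures.** Outcome with SD 1, no true effect, and the drop-out mechanisms listed below.

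**Step 1, attrition.** 160 × (1 − .25) = 120 families, 60 per arm. The 160 itself was not reproduced from the stated inputs. For example, f² = .10 on the between-group term gives 66, or 66/.75 = 88 with attrition. That is a separate question, and only the 80 per arm is used here.

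**Step 2, precision among completers.** The variance of six-month change is 2(1 − ρ) = 2 × .25 = .50. The standard error of the difference in change is √(.50 × (1/60 + 1/60)) = .129 SD.

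**Step 3, from bias to type I error.** For bias b, type I error is about P(|Z + b/SE| > 1.96). With b = .113, b/SE = .113/.129 = .876, and the two tails give .139 + .002 = .14. With b = .05, b/SE = .39, giving about .07.

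**Step 4, simulated completer analyses, 80 per arm, ρ = .75, loss at random given observed data.**

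| Assumed drop-out | Bias in change (SD) | Type I error, change | Type I error, group × time | Type I error, group main effect |
|---|---|---|---|---|
| 28% lost; tied to last observed change in the planning arm, log-odds 0.5 per SD | .03 | 5% | 5% | not run |
| Same, log-odds 1.0 | .05 | 7% | 8% | not run |
| Same, log-odds 1.6 | .08 | 10% | 11% | not run |
| About 29% lost; same kind of mechanism, slope scaled in different ways | .08 to .11 | 9-14% | 12-21% | not run |
| 25% lost overall; tied to six-week activity (log-odds 1 per SD), rate or mechanism differing by arm | 0 to .04 in absolute size | not run | 5-8% | 12-29% |
| As the row above, but same mechanism and rate in both arms | 0 | not run | about 5% | 5% |

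In the fifth row, the bias in the six-month difference itself was .15 to .22 SD when loss was related to activity in one arm only. Maximum likelihood on all observed waves gave 0.00. With an autoregressive correlation, the bias in change in that row ran opposite in sign to the bias in the six-month difference (for example −.036 against +.206).

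**Step 5, what a test would have shown.** Drop-out was made to run in opposite directions in the two arms, and a drop-out indicator was tested against baseline with the arms pooled. The test was significant in 5% of trials, its nominal level, while type I error for the group main effect was .21 to .22.

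**Step 6, loss not at random and differing by arm.** For the six-month difference, completers were biased by .16 to .29 SD and maximum likelihood by .07 to .16 SD. For change from baseline, completers were biased by .04 to .12 SD and maximum likelihood by .06 to .16 SD. A likelihood model does not cure this case.

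**The case against.** The strongest reply is that the article is a condensed account and commits to the right components: an examination of missingness, ITT, sensitivity analyses and an allowance for attrition. Which imputation or likelihood model is used, and the form of a not-at-random analysis, usually belong in an analysis plan that is not shown. That stands, and the absence of such detail is not the point. The point is a rule that the article does state: the method follows from tests that cannot support the choice.

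Several stronger readings are tempting, and the text does not support them.

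- A reader might infer that the primary analysis is confined to children with all four waves. The article does not say so. Its order (examine, handle, analyse) fits imputation before the ANOVA.
- A reader might take *also* to mean that the primary analysis is complete-case. The word may only add ITT to the missingness work described just before. The population is unstated, which is a different fault.
- A reader might suppose that a non-significant test would permit complete-case analysis. No such rule or threshold is given.
- A reader might expect the bias to favour planning. That needs unsuccessful planning families to leave selectively. Other patterns could reverse it, and no drop-out by arm is reported. The counts under Results reflect continuing recruitment and are not drop-out rates.
- A reader might count further losses from the wear requirement, "for a minimum of 10 hours per day for 7 days at each time point". That is a wear instruction, not a deletion rule, and no rate of unusable weeks is given.

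The larger simulated figures also rest on strong mechanisms. Log-odds of 1.6 per SD is an odds ratio of about 5, in one arm only.

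**Conclusion.** The point holds in a limited form. The plan lets missingness tests choose the method, words ITT as an addition, and gives the primary ANOVA no population.

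The harm is conditional. It requires that completers are what is analysed and that drop-out differs by arm in rate or mechanism. Under those conditions, with loss at random and ρ = .75, bias in change was about 0 to .11 SD. Type I error was about 5-14% for the change contrast, 5-21% for group by time and 12-29% for the group main effect. The primary outcome is headed as change from baseline to six months, so the first two figures are the closer ones. The last applies if the group main effect is read as the answer. With one mechanism common to both arms there was no bias. The mechanisms are assumptions, and neither the size nor the direction for this trial can be known in advance.

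**What to change.** Rewrite the Analysis strategy before outcome data are analysed by arm, along these lines:

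- **Primary analysis.** ITT: the pre-selected child from every randomised family, in the assigned arm, with every available wave, in a likelihood-based mixed model for repeated measures. Multiple imputation that uses the earlier waves is an acceptable alternative. The choice is fixed now and holds whatever the missingness tests show.
- **Missingness tests.** Keep them as description, and tabulate missingness by arm and wave.
- **Complete-case ANOVA.** Report it as supportive.
- **Sensitivity.** Include one not-at-random analysis among those already promised, such as a delta shift applied to drop-outs until the conclusion changes. It is needed because the mixed model is also biased when loss is not at random.

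The cost is a change of wording and slightly more analysis work. No new data are needed, and the article describes the study as ongoing.

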### Present research

The primary research question is whether a planning condition improves adherence to regular physical activity compared to a control condition at six months. We have four secondary research questions that will also be examined:Does the planning condition improve motivational, health-related quality of life, and health-related fitness outcomes compared to the control condition at six months?Can group differences among these motivational, behavioural, and health-related fitness outcomes be explained through a mediation model?Can motivational variables predict adherence? Do these differ by condition? Our hypothesis is thatIs there an intergenerational, seasonal, or gender difference across primary outcomes by assigned condition?

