### Hypotheses

We hypothesize that adherence will be higher for the planning condition in comparison to the more standard physical activity education condition. We also propose that the effect may wane over time from the initial measurement period but all outcomes will remain significantly higher at six months. We hypothesize that the planning condition will not affect intentions but will positively affect health related fitness and QOL. We also hypothesize that the covariance of the assigned conditions (planning, education) on use/adherence will be explained by planning and the use of behavioral regulation strategies (i.e., manipulation check). In turn, the covariance between planning and behavioral regulation strategies and health-related outcomes will be explained by physical activity adherence among conditions. In addition, affective attitude and perceived behavioral control will predict intention, intention will predict planning and planning will predict adherence across conditions. Finally, we hypothesize that children will show greater adherence to the planning condition than their parents. No differences in gender or season are hypothesized but these are exploratory research questions because there is limited research at present to make any definitive statement.

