### Statistical power and sample size

Based on our previous research, **160** families (80 per group) will be recruited to detect a small-medium effect size (f^2^ = .10; [52]) in adherence to physical activity (primary outcome) with a type one error of .05, an average correlation of .75 across time for our DV of interest, and a power of .80. Our sample size also considers the main 2 (group) x 2 (parent/child) x 4 (time) repeated measures design using G-Power [53] and a potential 25 % attrition rate similar to the pilot study. Finally, the evaluation of physiological outcomes of participants across time will follow a 2 (condition) x 2 (time) interaction. Physiological parameters have larger effect sizes than the social/psychological variables in the study due to smaller standard error scores. The proposed sample size is, therefore, more than adequate to ensure sufficient statistical power for the physiological measurements.

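### The primary question is the arm difference in children's activity change at six months, but the stated 2 x 4 repeated-measures ANOVA names neither a deciding term nor a six-month contrast

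*Protocol article*

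**What the plan says.** Two places in the Protocol article fix the target. Under Present research the primary question is "whether a planning condition improves adherence to regular physical activity compared to a control condition at six months". Under Outcome measures the primary outcome is headed "Change from baseline in children’s physical activity to 6 months", and the measurement schedule reads "Children’s physical activity will be assessed at four separate time points: baseline, six-weeks, three-months and six-months". Baseline is therefore one of the four times.

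Under Analysis strategy the first research question is to be "analyzed using a 2 (condition) x 4 (time) repeated measures factorial ANOVA on the primary outcome of child adherence", for one randomly chosen eligible child per household. The next step is "Post hoc examinations using Tukey follow-up procedures will be utilized if necessary". The section does not say whether the condition main effect or the condition-by-time interaction decides the trial. It names no six-month contrast, no family for the Tukey comparisons and no baseline covariate.

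Under Hypotheses the authors expect that "the effect may wane over time from the initial measurement period but all outcomes will remain significantly higher at six months".

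**The concern.** A 2 x 4 repeated-measures ANOVA offers two terms that involve condition, and neither is the six-month comparison.

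- The condition main effect compares the arms averaged over all four visits, including the visit before randomisation, when no effect can exist.
- The condition-by-time interaction has 3 degrees of freedom and responds to any difference in time profile, whether at six weeks, three months or six months.

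The six-month comparison appears only if a Tukey follow-up is judged necessary. A Tukey test between arms at that visit compares raw means and ignores each child's baseline value.

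At stake is what a positive or negative primary result would mean. With the interaction as the deciding term, a significant result does not establish a six-month difference. With the main effect or a Tukey pair deciding, a real six-month difference is easily missed. Because the rule is not stated, it could also be settled after the results are seen.

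**Working it through.** **Inputs from the documents.** Statistical power and sample size gives 160 families, 80 per group, 25% attrition, correlation .75 across time and type one error .05. Completers: 160 x .75 = 120, or n = 60 per arm.

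**Assumptions.** The article gives no standard deviation, so effects are in SD units (SD = 1). The covariance is compound symmetric with correlation rho = .75, and .50 is also tried.

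**The plan's own figure.** The total of 160 was not reproduced. With f = .10 the interaction needs 70 families (94 after attrition) for two groups and 101 (135) for four. With f = sqrt(.10) the between-group effect needs 66 (88). A regression with f-squared = .10 and 3 df needs 114 (152). That is a separate matter; only n = 60 per arm is used below.

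**Formulas.** Let d0 to d3 be the arm differences at baseline, six weeks, three months and six months, with mean m. The noncentrality parameters are:

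- interaction (3, 354 df): (n/2) x sum of (d - m)^2 / (1 - rho)
- condition main effect (1, 118 df): (n/2) x m^2 / [(1 + 3 rho)/4]
- six-month change score (1, 118 df): (n/2) x d3^2 / [2(1 - rho)]
- six-month value adjusted for baseline (1, 117 df): (n/2) x d3^2 / (1 - rho^2)

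**Effect that fades to nothing: 0, .50, .25, 0 SD.** Here m = .1875 and the sum of squares is .1719.

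- Interaction, rho .75: 30 x .1719/.25 = 20.6, significant in 97.7% of trials.
- Interaction, rho .50: 30 x .1719/.50 = 10.3, significant in 77%.
- Six-month test, change score or baseline-adjusted: noncentrality 0, so 5%.

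With the milder pattern .40, .20, 0 SD the interaction is significant in 87.2% (rho .75) or 55.7% (rho .50).

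**Sustained effect: 0, .34, .34, .34 SD, rho .75.** Here m = .255 and the sum of squares is .0867.

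| Deciding test | Noncentrality | Power |
|---|---|---|
| Six-month, baseline-adjusted | 30 x .1156/.4375 = 7.93 | 80% |
| Interaction | 30 x .0867/.25 = 10.4 | 77% |
| Six-month change score | 30 x .1156/.50 = 6.94 | 74% |
| Condition main effect | 30 x .0650/.8125 = 2.40 | 34% |

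If the .34 SD appears only at six months, m falls to .085 and the main effect has 8% power.

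**Tukey comparison of raw six-month means, .34 SD.** The expected t is .34/sqrt(2/60) = 1.86. For a family of all 8 cells (28 pairs) the critical t is 3.05 and power is 12%. For the six-month pair alone the critical t is about 1.97 and power is 46%.

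**Effect that wanes but persists: 0, .50, .40, .30 SD, rho .75.** Here m = .30 and the sum of squares is .14. The interaction has noncentrality 16.8 and 94% power. The baseline-adjusted six-month test has 30 x .09/.4375 = 6.17 and 69%.

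**Gain from baseline as a covariate.** The variance factor is .4375 against .50 for change scores at rho .75, a saving of 12.5%. At rho .50 it is .75 against 1.00, a saving of 25%.

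**The case against.** The best defence is that the interaction is the natural reading. The sample-size section itself speaks of a condition-by-time interaction for the physiological outcomes. Because baseline is a time level, that term compares changes between arms. For a sustained effect it loses little (77% against 80%), and for a waning effect that persists it is the more powerful test. This stands. It limits the point but does not remove it, because a significant 3-df interaction still does not locate the difference at six months, and Analysis strategy does not name the interaction as the deciding term.

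Four stronger readings are tempting and are not supported.

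- A reader might infer that the plan is exposed to false success and to a missed effect together, at the sizes above. The two arise under different deciding terms. If the eight-cell Tukey pair decided, a true null at six months would be rejected in only about 0.25% of trials.
- A reader might infer that the ANOVA does not handle baseline at all, or cannot address change. That is wrong for the interaction, where the loss is efficiency. It is right for the main effect and for the raw six-month comparison.
- A reader might take fading to zero as the authors' expectation. Hypotheses foresees waning but a persisting six-month difference, so that pattern is a stress case.
- A reader might take 28 Tukey pairs as given. The article states no family, hence the range.

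It can also be said that contrasts and covariance structure belong in an analysis plan that is not shown. Covariance detail does. But the article itself names the primary test, its factors and its follow-up, and that stated method does not isolate the stated question.

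**Conclusion.** The point holds as a mismatch between question and test. What it costs depends on which term decides, which the article leaves open. Under the interaction, the weakness is interpretation: significance in 77% (rho .50) to 97.7% (rho .75) of trials in the stress case with no six-month effect, with little power lost for a sustained one at rho .75. Under the main effect or a Tukey comparison, the weakness is power: 34%, or 12% to 46%, against 80% for a baseline-adjusted six-month test.

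These sizes rest on assumed SD effects, compound symmetry and 60 completers per arm. The mismatch itself rests only on the article's wording. Since the primary conclusion depends on it and no new data are needed to cure it, it should be settled before the final analysis.

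**What to change.** Prespecify one primary test at two-sided alpha .05: the planning-minus-control difference in the child's accelerometer activity at six months, adjusted for baseline. Estimate it from a mixed model for repeated measures with baseline as a covariate, or from a constrained longitudinal model with a common baseline mean. Report the six-week and three-month contrasts and the omnibus condition-by-time interaction as secondary, and drop the Tukey step from the primary question.

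The cost is analysis wording only. The drawback is that the omnibus interaction loses primary status, and it would have more power if the effect is larger early (94% against 69% for .50, .40, .30 SD), though for a different question from the one the article calls primary.

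### If correlation falls with time lag, the 2 x 4 repeated measures ANOVA is mildly liberal and its pooled error understates the variance of six-month change, the primary outcome

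*Protocol article*

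**What the plan says.** Under Analysis strategy, the protocol article assigns the first research question to a "2 (condition) x 4 (time) repeated measures factorial ANOVA on the primary outcome of child adherence", and adds: "Post hoc examinations using Tukey follow-up procedures will be utilized if necessary". One eligible child per household enters this analysis. Multilevel modelling is named there only for parent/child dependence, not for covariance across waves.

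The primary outcome is headed "Change from baseline in children’s physical activity to 6 months" and is measured at "four separate time points: baseline, six-weeks, three-months and six-months".

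Statistical power and sample size plans on "an average correlation of .75 across time for our DV of interest", "with a type one error of .05" "and a power of .80". It gives no lag pattern and no standard deviations. The Analysis strategy extends variants of the same design to the secondary questions.

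**The concern.** A classical repeated measures ANOVA judges every within-family comparison against one error mean square. That is exact only under sphericity, meaning that the differences between any two waves all have the same variance. The gaps here run from 6 to 26 weeks. If measurements further apart correlate less, the pooled error is an average: too large for adjacent waves and too small for the widest gap. The widest gap is baseline to six months, which is the primary outcome. The standard Tukey procedure uses the same mean square, and planning on one average correlation fits this pooled-error reading.

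At stake are a somewhat liberal omnibus test and a confidence interval for six-month change that is too narrow.

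**Working it through.** **Inputs from the article:** alpha .05; average correlation .75; 80 families per group with 25% attrition, so 80 x .75 = 60 per arm; four waves, taken as weeks 0, 6, 13 and 26.

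**Assumptions:** equal variances; normal data; where correlation decays, it falls with weeks apart while the six pairwise correlations still average .75; Tukey is applied to the six pairwise wave differences in the condition effect.

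**Step 1, the plan's own figure.** With a common correlation of .75 the condition by time F test is exact at .05. Simulation of 40,000 null trials gave .0499 at 80 per arm and .0497 at 60 per arm. The stated .05 is reproduced.

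**Step 2, error variance for six-month change.** With wave variance s², the pooled error implies a variance of 2s²(1 - .75) = .50s² for any change between two waves. The true variance of the 0-to-26-week change is 2s²(1 - r), where r is the correlation between those two waves.

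| Assumed range of correlations | r (0 to 26 weeks) | True variance / s² | True / pooled | SE ratio, pooled / true |
|---|---|---|---|---|
| all .75 | .75 | .50 | 1.00 | 1.00 |
| .67 to .81 | .67 | .66 | 1.32 | .870 |
| .61 to .86 | .61 | .78 | 1.56 | .801 |
| .58 to .88 | .58 | .84 | 1.68 | .772 |

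The pooled-error interval is therefore about 13%, 20% and 23% too narrow in the three decay cases.

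**Step 3, type I error of the contrast on the pooled error.** The approximate rate is 2 x (1 - Φ(critical value x SE ratio)).

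- Unadjusted, critical value 1.96: the products are 1.71, 1.57 and 1.51, giving about 8.8%, 11.7% and 13.0%.
- Tukey over four waves, critical t 2.58: the products are 2.24, 2.07 and 1.99, giving about 2.5%, 3.9% and 4.7%. With equal correlations the same critical value gives about 1.0%, which is this contrast's per-comparison share.

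**Step 4, simulation** (40,000 null trials per case, 60 per arm).

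| Correlations | Omnibus F, uncorrected | Six-month contrast, pooled error, unadjusted |
|---|---|---|
| all .75 | 5.1% | 5.0% |
| .67 to .81 | 5.5% | 8.6% |
| .61 to .86 | 6.2% | 11.6% |
| .58 to .88 | 7.0% | 13.1% |

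A separate run of 8,000 trials put the mildest decay case at about 5.2% for the omnibus test. With Tukey, the six-month contrast rejected in 2.4-4.8% of trials over the three decay patterns, and the familywise rate was 5.4-6.7%. When the standard deviation was also allowed to rise over time to 1.25-1.5 times baseline, the Tukey-tested contrast reached at most 5.8%. The contrast on its own error gave 4.9-5.4% in every equal-variance case. In other runs with falling correlation, the Greenhouse-Geisser test gave 4.7-5.0% and the multivariate test 4.8-5.2%.

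**Step 5, a pattern in the other direction.** Put the 0-to-26-week correlation at .85 and the other five at .75. The mean is (5 x .75 + .85)/6 = .767, and the variance ratio is (1 - .85)/(1 - .767) = .64. The unadjusted pooled contrast then rejects in about 1.5% of null trials, so it is conservative.

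**The case against.** The article does not call the ANOVA univariate, state a pooled error term, or exclude a sphericity correction or the multivariate test. Such detail is commonly left to a full protocol or analysis plan that is not shown. This stands: silence about a correction is no finding. What remains is the method and follow-up that are named, for which the pooled-error reading is natural though inferred. A Greenhouse-Geisser correction stated elsewhere would repair only the omnibus test. It changes degrees of freedom and leaves the error term of the follow-up comparison as it was.

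A reader might infer that unequal spacing itself breaks the test, so that the planned .05 is not delivered, worst of all for six-month change. The documents do not support that. Unequal spacing does not violate sphericity; a non-spherical covariance does, and the article gives none. Nor do the 8-13% rates describe the documented procedure: they belong to an unadjusted contrast, whereas the article names Tukey. The near-5% Tukey result, however, comes from a multiplicity penalty offsetting an understated standard error, and the variance itself stays wrong.

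If follow-up tests run only after a significant omnibus test, then under the complete null the contrast cannot reject more often than the omnibus. This too is correct. It does not carry over to an early effect that has vanished by six months, an extreme form of the waning expected under Hypotheses. There, neither gating nor corrected omnibus degrees of freedom protects an unadjusted pooled contrast, while the contrast on its own error held 4.7-5.6% across all cases simulated.

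Finally, these rates are non-directional. By symmetry only about half of the false positives would favour planning.

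**Conclusion.** A conditional and modest weakness in the error term. It needs two things that the article does not establish: correlation that falls with lag, and no correction or contrast-specific error. Given both, and an average correlation of .75, the omnibus error is about 5.2-7% and the pooled variance for six-month change is about 1.3-1.7 times too small. The Tukey-tested contrast stays at or below about 5-6%, against a share of about 1%. Under equal correlations there is no inflation, and under some patterns the pooled contrast is conservative. The point is worth acting on because the affected comparison is the primary outcome and the better method costs almost nothing.

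**What to change.** In Analysis strategy, state that child activity will be analysed with a repeated-measures mixed model with unstructured covariance over the four waves, and that the condition difference in baseline-to-six-month change will be tested with its own standard error. If the ANOVA is kept, use Greenhouse-Geisser or multivariate tests for the omnibus effect, and contrast-specific error terms for follow-up comparisons in place of the pooled mean square. Apply the same to the secondary outcomes measured at four waves.

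The cost is one sentence of wording and standard software, with no new data or families. The six-month interval becomes somewhat wider if correlation does fall with lag.
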